**Rehabilitation**

After an upper limb fracture, patients are often referred to physiotherapy for rehabilitation, aiming to reduce pain, improve the range of motion, and progressively gain muscle strength in both surgical and conservative cases. Although these interventions have clear objectives, their approaches vary significantly and may include thermal modalities, electrophysical resources, manual therapy, kinesitherapy, application of dynamic orthoses, guidance, and education (Peluso et al., 2022).

Rehabilitation protocols following proximal humeral fractures (PHF) are not well defined in the literature. A recent systematic review (Schnackers et al., 2019) highlighted the scarcity of detailed physiotherapy protocols based on scientific evidence aimed at restoring patients' daily activities. Among the evaluated studies, the ProFHER clinical trial (PROximal Fracture of the Humerus Evaluation by Randomisation), published in 2015 (Handoll et al., 2015), was the only one to provide a complete description in this regard.

The ProFHER physiotherapy protocol progresses in phases. The timeline of these phases depends on various factors: age, fracture healing stage, pain tolerance, patient expectations, activity level, and general health. If the fracture is stable, phase 3 begins after sling removal at three weeks, and phase 4 starts three weeks later. Most patients regain functional status within six weeks, achieving independent shoulder function.

In 2019, Ratajczak et al. emphasized that the ideal treatment for PHF depends on the type of fracture, patient expectations, physical fitness level, and acceptance of the proposed treatment. They recommended adjusting exercises based on the fracture's stability and the patient's abilities and expectations. For surgical cases, they indicated that rehabilitation should begin immediately after immobilization removal, typically between the fourth and ninth weeks. Rehabilitation, according to the authors, should include passive exercises, active-passive exercises, and monitored active isometric, concentric, and eccentric exercises as the limb's function improves. They proposed a three-stage postoperative rehabilitation program using kinesitherapy:

**Stage 1: First 3 weeks**

- Immobilization with a sling on the operated limb without weight-bearing (except for arthroplasty).
- Initiation of pendulum exercises.
- Assisted passive movements.
- Avoid external rotation during the first 6 weeks.

**Stage 2: Third to ninth week (provided there are no abnormalities in healing or secondary fragment displacement):**

- Assisted active exercises, flexion, and abduction of the shoulder joint.
- Careful active exercises with limb abduction until pain occurs, with no weight-bearing in the first 6 weeks. Gradually add weight.

**Stage 3: After the ninth week**

- Isotonic, eccentric, and concentric exercises.
- For patients with radiographic fracture healing and joint contracture, passive stretching exercises with an experienced professional are recommended.

Monticone et al. (2021) compared the effectiveness of task-oriented exercises based on patients' specific work activities and occupational therapy versus conventional exercises. They found superior results in reducing disability, pain, and improving quality of life in patients after surgery for PHF. After early mobilization (at the end of the first postoperative week), basic exercises were introduced to improve glenohumeral mobility and muscle awareness in the upper limb. Patients learned techniques to progressively gain resistance, speed, strength, and complexity in the standard movements of the muscles involved in the injury.

Subsequently, exercises based on patients' specific work activities were introduced, including moving objects of different shapes and sizes in various directions, picking up objects from a table in different positions, assembling complex items by mixing components arranged on a table, and catching objects thrown at different heights and speeds. Additional exercises aimed to recover dexterity, balance, and other functional demands, such as transitioning from a sofa to a seated position, standing up from a chair, walking and turning at a preferred speed, and ascending and descending stairs and obstacles. Occupational therapists also provided guidance on sling care and ergonomic principles based on patients' pre-fracture activities.

As mentioned earlier, rehabilitation after fractures may also involve using electrophysical resources, including light sources.

**Photobiomodulation**

Photobiomodulation (PBM), formerly known as low-level laser therapy, is defined as the use of light sources to stimulate healing, relieve pain, and reduce inflammation (Hamblin, 2017). This therapy is safe, minimally invasive, and has no side effects (Hamblin, 2017; Sharma et al., 2023). The most commonly used sources for PBM are lasers and LEDs (light-emitting diodes) of low intensity or power in the red (600–700 nm) and near-infrared (770–1200 nm) wavelengths.

PBM action is based on light absorption by cellular chromophores, which can be categorized into three groups: mitochondrial cytochromes (proteins bound to the inner mitochondrial membrane, such as cytochrome C oxidase); opsins (3 and 4); and heat- or light-sensitive calcium ion channels, and nano-structured water clusters (Sharma et al., 2023). Light-sensitive ion channels are activated by light absorption by opsins, while mitochondrial cytochromes absorb red and near-infrared wavelengths. Light above 980 nm is likely absorbed by nano-structured water clusters, activating transient receptor potential (TRP) ion channels. Heat-sensitive TRPs may also be activated by minor temperature changes (Sharma et al., 2023).

Red or infrared light absorbed by mitochondrial cytochrome C oxidase may dissociate the inhibitory nitric oxide associated with it, increasing enzymatic activity, electron transport, mitochondrial membrane potential, and ATP production (Sharma et al., 2023). Another possible explanation for PBM effects is the activation of light-sensitive ion channels, allowing calcium influx into cells or mitochondria. Both pathways activate mitochondrial metabolism and numerous signaling pathways, such as reactive oxygen species (ROS), cyclic AMP, nitric oxide, and calcium ions. These pathways lead to transcription factor activation, enhancing gene expression related to protein synthesis, cell migration, proliferation, anti-inflammatory signaling, anti-apoptotic proteins, and antioxidant enzymes (de Freitas & Hamblin, 2016; Sharma et al., 2023).

Regarding PBM use in limb fracture treatment, a systematic review and meta-analysis published in 2020 highlighted the lack of randomized controlled trials (RCTs) on this topic, including only two low-evidence studies. Combined analysis of these RCTs revealed clinically and statistically significant differences favoring PBM in improving fractured limb function and significantly reducing pain. However, no differences were found regarding radiographic fracture healing (Neto et al., 2020). The review also emphasized the need for new RCTs following CONSORT (Consolidated Standards of Reporting Trials) recommendations, aiming to determine the best dosimetric parameters and evaluate potential adverse effects. Other reviews assessing PBM's role in bone repair using diverse methodologies concluded that PBM might accelerate bone regeneration. However, standardizing parameters and treatment protocols remains necessary (Deana et al., 2018; Escudero et al., 2019; Cheng et al., 2020).

Subsequently, Saebo et al. (2021) evaluated the effect of PBM applied during the plaster immobilization period (conservative, non-surgical treatment) on pain and stiffness in patients with distal radius fractures. In a double-blind RCT, 53 participants received nine PBM applications (904 nm, 25W pulse peak, 60 kHz, 60 mW average power, 6.6 J per session) and were assessed at 4, 8, 12, and 26 weeks post-trauma. The PBM-treated group showed significantly better results than the placebo group in range of motion and grip strength throughout the assessment period, with statistically significant differences observed after 4 weeks. The discrepancies between the injured and uninjured wrists of each patient were significantly smaller in the PBM group for grip and pinch strength at weeks 4 and 26. Additionally, significantly fewer patients in the PBM group reported nighttime pain during the third week of follow-up compared to the placebo group. However, no differences were found between the PBM and placebo groups in standardized wrist function and pain perception questionnaires, analgesic use, or local edema.

The same group of authors assessed the effect of PBM (904 nm, 25W pulse peak, 60 kHz, 60 mW average power, 7.2 J per session, 1.2 J per point), combined with exercises, applied after immobilization removal in 50 patients with distal radius fractures treated conservatively (non-surgically). The triple-blind RCT evaluated standardized wrist function and pain perception questionnaires, nighttime pain, and analgesic consumption at 4, 8, 12, and 26 weeks. Nighttime pain and analgesic use were also assessed after 7 weeks. The PBM group showed significantly better outcomes in standardized function and pain perception questionnaires at 8, 12, and 26 weeks. Nighttime pain and analgesic use were significantly lower in the PBM group between 7 and 26 weeks (Saebo et al., 2022).

Jana Neto et al. (2023) evaluated the effect of PBM with LEDs on the healing process of soft tissue injuries associated with surgically treated tibia fractures. The study included 27 adult individuals awaiting resolution of soft tissue injuries before definitive surgery. PBM (144 LED diodes at wavelengths of 420 nm, 660 nm, and 850 nm, 3 J per point, for 10 minutes) was applied daily until the soft tissues were ready for definitive surgery. The control group was treated with inactive devices identical in appearance. The PBM-treated group showed better daily healing rates, greater average daily reduction in pain scores, four times fewer infections at the pin sites of external fixators, and faster resolution (10 days earlier). No adverse effects were reported.

**Evaluation of Therapeutic Success in PHF Treatment**

Even after surgical or conservative treatment, PHF can still cause pain, limitations in daily activities, limb disability, and reduced quality of life. Clinical trials on PHF often report diverse outcomes, complicating treatment comparisons and consensus development (Nowak et al., 2019; Richard et al., 2020).

It has been suggested that the evaluation of therapeutic success in PHF treatment should primarily reflect the restoration of patients' daily activities, using tools known as Patient Reported Outcomes (PRO). For PHF follow-up, it is recommended to include at least one functional score (e.g., DASH - Disabilities of the Arm, Shoulder, and Hand; ASES - American Shoulder and Elbow Surgeon’s Score; or Oxford Shoulder Score) and PROs reflecting health status and quality of life, such as the EQ-5D - EuroQol-5 Dimension and the SF-6D - Short Form-6 Dimension (Nowak et al., 2019; Richard et al., 2020).

The DASH functional disability index, developed in 1996, is a self-administered instrument for measuring symptoms and physical function of the upper limbs. It can be used for clinical and research purposes. The DASH consists of questions related to daily activities, symptoms, and social/role functions over the past week. The 30 questions are scored on a scale of 1 to 5 points, with a total score ranging from 0 (no difficulty) to 100 (significant difficulties/disabilities) (Hudak et al., 1996). This tool has been adapted into over 50 languages and extensively validated in numerous scientific articles (Kennedy & Beaton, 2017; Richard et al., 2020). DASH has demonstrated strong reliability, moderately strong validity, and high psychometric properties in evaluating PHF patients (Slobogean et al., 2010; van de Water et al., 2014).

A shorter version, Quick DASH, was released in 2005, containing 11 items (Beaton et al., 2005). Like the original version, Quick DASH offers five response options and a total score of 100 points. Both questionnaires have optional modules, scored separately, designed for athletes/performers and work-related assessments (Kennedy & Beaton, 2017). Quick DASH can replace DASH for evaluating upper extremity disorders with similar accuracy, offering easier and faster administration (Beaton et al., 2005; Gummesson et al., 2006).

The Brazilian version of DASH was validated in 2006 (Orfale et al., 2006), while Quick DASH was more recently validated (da Silva et al., 2020), proving to be reliable, responsive, and a viable alternative to DASH for evaluating upper extremity dysfunctions related to orthopedic and traumatic injuries.

EQ-5D and SF-6D have shown strong reliability and moderately strong validity in PHF patients. EQ-5D also demonstrated good responsiveness and was recommended as a tool for assessing health-related quality of life in PHF patients in a systematic review (Olerud et al., 2011; Rabi et al., 2015; Richard et al., 2020).

EQ-5D-3L comprises five health domains (mobility, self-care, usual activities, pain/discomfort, anxiety/depression), each with three levels (no problems, some problems, extreme problems). Additionally, it includes a visual analog scale (VAS) where participants rate their health status from 0 ("Worst possible health state") to 100 ("Best possible health state"), generating 243 possible health states (EuroQol, 2010).

The SF-6 is derived from the Brazilian-adapted version of the SF-36 questionnaire (Medical Outcomes Study 36-Item Short-Form Health Survey), which has been evaluated in over 200 diseases and translated into 40 countries (Ware & Sherbourne, 1992; Garrat et al., 2002; Campolina et al., 2011).

**2. JUSTIFICATION**

There is substantial evidence highlighting the capacity of photobiomodulation (PBM) to control pain and assist in tissue repair. However, in the treatment of fractures, there is a need to develop randomized controlled trials (RCTs) with high methodological rigor to establish the best parameters and outcomes for PBM. In the case of PUF, besides the importance of finding the best dosimetric parameters for PBM application, there is a need to standardize the outcomes to be evaluated to obtain a gold standard treatment. This is because the majority of PUF cases present a slow recovery period accompanied by pain and functional limitations.

This study aims to assess the effects of PBM, using a home-based LED device with parameters supported by the literature, primarily concerning post-operative recovery of function and pain relief in surgically treated proximal humerus fractures. The study will be conducted in a controlled, randomized, and double-blind manner.

Hypotheses:

H0: Photobiomodulation is not effective in the post-operative phase of PUF.

H1: Photobiomodulation is effective in the post-operative phase of PUF.

**3. GENERAL OBJECTIVE**

The general objective of this study is to evaluate the effects of photobiomodulation (PBM) on the functional recovery of proximal humeral fractures treated with open reduction and internal fixation (ORIF) and stabilized with fixed-angle plates.

**3.1. Primary Objective**

The primary outcome of the study is to assess the functional recovery following proximal humeral fractures treated with ORIF, stabilized with fixed-angle plates, and managed with physiotherapy and photobiomodulation. This will be evaluated using the Brazilian version of the Quick DASH (Disabilities of the Arm, Shoulder, and Hand) questionnaire.

**3.2. Secondary Objectives**

The secondary outcomes will evaluate the effects of PBM applied after proximal humeral fractures treated with ORIF, stabilized with fixed-angle plates, and managed with physiotherapy on:

- Shoulder range of motion (ROM), assessed over time and compared with the unaffected limb.
- Muscle strength, measured over time and compared with the unaffected limb.
- Intensity of spontaneous pain and pain during limb function.
- Occurrence of nighttime pain.
- Pressure pain at the fracture site.
- Analgesic consumption.
- Fracture consolidation.
- Quality of life.
- Incidence of adverse events.
- Direct and indirect costs associated with the procedures performed during the study period, for subsequent cost-effectiveness analysis of the intervention.

**4. MATERIAL AND METHODS**

This is a parallel, double-blind, randomized controlled clinical trial. The study design will adhere to international recommendations for randomized clinical trials outlined in the SPIRIT (Standard Protocol Items: Recommendations for Interventional Trials - Chan et al., 2013) protocol, as shown in Figure 1, and the regulatory norms for research involving human subjects established by the National Research Ethics Committee (CONEP).

This research project will be submitted to the Research Ethics Committee of Universidade Nove de Julho (UNINOVE), and participants will sign the informed consent form after receiving all necessary explanations (APPENDIX 1). The protocol will be registered on the Clinical Trials platform (<https://clinicaltrials.gov/>). The study report will be conducted in accordance with the CONSORT (Consolidated Standards of Reporting Trials) guideline. The study flowchart is presented in Figure bellow.

###
[figure not shown]

**4.1 Study Location and Sample Selection**

The surgical procedures, outpatient follow-ups, and physiotherapy will be conducted at the Orthopedics and Traumatology Clinic of [name] Netto Hospital (HMACN), part of the Municipal Health Department of São Paulo, Brazil, between April 2024 and December 2025.

**4.2 Research Team**

The research team will consist of:

- **1 Researcher**: Responsible for preparing the randomization process and envelopes to ensure allocation confidentiality. This researcher will not participate in any evaluations.
- **1 Researcher (medical resident)**: Responsible for retrieving the allocation envelope upon participant enrollment, delivering the appropriate PBM equipment (active or placebo), and providing instructions for home use.
- **4 Surgeons with experience in proximal humerus fractures (PHF)**: Responsible for all surgical procedures and participant eligibility evaluations.
- **4 Blinded Orthopedic Medical Examiners**: Responsible for all evaluations, from postoperative assessments to outpatient follow-ups, while remaining blinded to the experimental group of each participant.
- **1 Principal Researcher**: An orthopedic physician aware of group allocations during the data collection phase and responsible for coordinating data collection. This researcher will not participate in any evaluations and will oversee data interpretation.
- **1 Physiotherapist (blinded to the experimental group)**: Responsible for accompanying participants during all sessions.
- **3 Medical Residents (blinded to the experimental group)**: Responsible for daily contact with participants to monitor PBM device usage, provide guidance, and address any questions.

**4.3 Examiner Calibration and Training**

The training and calibration process for the four researchers conducting postoperative evaluations will include three joint practice sessions with one volunteer who will not be part of the experimental groups. The data collected during these sessions will be discussed among the researchers to achieve excellent agreement levels. Subsequently, each examiner will independently perform the proposed measurements on ten adult volunteers who will also not be part of the study sample. The data collected will be analyzed using the Intraclass Correlation Coefficient (ICC) test (Fleiss, 1986). Once the agreement among examiners is rated as excellent, the measurements will be applied to the study participants.

**4.4 Participant Characterization**

Participants of both genders admitted to HMACN with isolated, closed proximal humerus fractures requiring surgical treatment and treated with ORIF using a locked angular stability plate for the proximal humerus (Neer 1070, Carrera et al., 2012; Petros, 2019) will be included according to the following eligibility criteria.

**Inclusion Criteria:**

- Participants aged 18 to 65 years of both genders, with PHF classified as:
  - Neer group III
  - Neer group IV
  - Neer group V
  - AO/OTA subgroups A2 and A3
  - AO/OTA group B
  - AO/OTA group C (only in patients younger than 55 years).

**Exclusion Criteria:**

- Individuals with prior injuries or sequelae in the shoulder or scapular girdle, or motor deficits due to central or peripheral neurological injuries.
- Patients with pathological fractures.
- Participants with postoperative infection or implant loosening.
- Those with ipsilateral fractures in other areas of the limb.
- Patients with neurovascular injuries causing sensory deficits at the injury site.
- Individuals with local or systemic conditions contraindicating surgical intervention or complicating the postoperative period.
- Participants with a history of photosensitivity.
- Individuals with neurological or psychiatric disorders.
- Those with proliferative or infectious skin lesions in the shoulder area where LED light will be applied.
- Participants who used anti-inflammatory medications within 5 days prior to the trauma.
- Pregnant individuals.
- Participants who experience surgical complications, such as neurological or vascular injuries or fracture line extension during surgery, as they will not meet the desired progression criteria.

Such participants will be excluded from statistical analyses but will have their data collected and documented.

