**4.7 Randomization and Allocation Concealment**

The sequence generation and envelope preparation will be conducted by a researcher not involved in the study.

Participants will be randomly assigned to the two experimental groups using a random sequence generator (<https://www.randomizer.org/tutorial/>), with the option for block randomization of six participants, forming seven blocks. Opaque envelopes will be numbered sequentially, each containing a sheet with the corresponding experimental group based on the generated order. The envelopes will be sealed and stored in numerical order in a secure plastic container.

Participants meeting all previously described eligibility criteria will be evaluated by four surgeons and included in the study. All participants will undergo the same surgical protocol. The allocation envelope will be opened 24 hours after the surgical procedure when the PBM device is delivered. The device delivery will be performed by the medical resident researcher, who will be aware of the allocations.

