**4.8 Initial Procedures and Participant Recruitment**

Participants will be recruited from patients presenting to the emergency room at [name] Netto Hospital (HMACN) with shoulder trauma and suspected fractures. All patients will receive treatment according to the hospital's standard protocol.

The cases will be evaluated by the on-call orthopedic team, which will notify the research team. In the emergency room, the examining researchers will request standard imaging tests, including anteroposterior, scapular profile, and axillary shoulder radiographs, and CT scans when indicated. Preoperative tests, including complete blood count, coagulation profile, blood typing, serum levels of sodium, potassium, urea, creatinine, glucose, electrocardiogram, and chest X-rays (posteroanterior and lateral views), will also be requested. Echocardiograms and consultations with other specialties will be requested when necessary.

Potential study inclusion will be determined only after clinical and radiographic evaluations confirm eligibility. Participants will receive verbal and written explanations regarding the study's objectives and methods. Those who agree to participate will sign the informed consent form (Appendix 1).

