**4.9 Medication Prescription**

During hospitalization, analgesic prescriptions will include dipyrone 1g IV every 6 hours and tramadol hydrochloride 100 mg IV every 8 hours, maintained for the first 24 hours. If rescue analgesics are needed, the first option will be to administer tramadol hydrochloride 100 mg IV every 6 hours. Morphine sulfate will be the second rescue drug, administered at a dose of 2 mg IV up to every 8 hours. Patients will be reassessed for adjustments to the standard analgesic regimen, transitioning to "as needed" prescriptions for opioids when possible. All analgesic drug use will be documented. Corticosteroids or anti-inflammatory drugs will not be prescribed.

Upon discharge, participants will be prescribed dipyrone 1g orally every 6 hours for 5 days and tramadol hydrochloride 50 mg orally every 8 hours (if needed) for a maximum of 5 days. Participants will be instructed to use tramadol hydrochloride only if pain persists with dipyrone or in cases of moderate pain (4–7 on the pain scale). Participants reporting anti-inflammatory or corticosteroid use will be excluded from statistical analysis, and the case will be documented and discussed.

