**4.12 Photobiomodulation (PBM) Application**

PBM will be administered using LED devices in the form of a shoulder brace. Applications will commence 24 hours after surgery and will continue daily throughout the experimental period. Participants will perform the applications at home, receiving guidance on how to wear and operate the equipment upon hospital discharge, along with written instructions (Appendix 9). Each application will last 10 minutes.

The shoulder brace, manufactured by Cosmedical (Mauá, SP, Brazil), contains 159 red LEDs and 159 infrared LEDs arranged alternately. The area corresponding to the fixation plate, with a 2 cm safety margin added along its entire length, will not be irradiated (LEDs will not be placed there) to avoid potential heating of the plate from energy absorption.

Participants allocated to the control group will receive a device identical to the active one. However, only the activation plug light and sound will turn on when the button is pressed, leaving the internal LEDs deactivated

[figure not shown]

Figure . Design (A) and model (B) of the shoulder brace for PBM application.

Literature reports on the use of PBM after bone fractures indicate the use of red and infrared light sources with varying dosimetric parameters (Table 1), with radiant exposures ranging from 3 to 16 J/cm². The study by Chang et al. (2014), which served as the basis for the sample size calculation in this project, demonstrated positive effects of PBM on functional recovery of wrist and hand fractures using the Quick DASH questionnaire, with a radiant exposure of 9.7 J/cm². Accordingly, this project adopted radiant exposures of 10 J/cm² and 12 J/cm²

| **Wavelength (nm)** | **Power (mW)** | **Irradiance (mW/cm²)** | **Time (sec)** | **Radiant Exposure (J/cm²)** | **Radiant Energy (J) per Point** | **Number of Applications** | **Application Points** | **Results** | **Authors** |
| --- | --- | --- | --- | --- | --- | --- | --- | --- | --- |
| 830 | - | - | - | 8 and 16 | - | Once per day | Sensitive points | Earlier symptom resolution and ambulation | Chauhan & Sarin (2005) |
| 830 | 60 (average power) | 16.2 ± 1 | 600 | 9.7 | 2.5 | 10 | 1 | Pain relief and improved consolidation in conservative wrist fracture treatment | Chang et al. (2014) |
| 808 & 650 | 300 & 100 | 30 ± 20 | 20 ± 30 | 6 ± 3 | 6 ± 3 | 1 | 10 to 12 | Less opioid consumption in tibia fracture treatment | Nesioonpour et al. (2014) |

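### The drug criterion at entry (section 4.4) and the drug exclusion from analysis (section 4.9) differ in drug class and period, so a patient can be randomised and then dropped for use knowable before allocation

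*Protocol*

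**What the plan says.** Three parts of the Protocol bear on this.

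- **Entry (section 4.4, Exclusion Criteria).** The only drug criterion bars "Participants who used anti-inflammatory medications within 5 days prior to the trauma". The window ends at the trauma, and corticosteroids are not named.
- **Medication and analysis (section 4.9).** The paragraph on the hospital stay ends with "Corticosteroids or anti-inflammatory drugs will not be prescribed". The next paragraph opens with "Upon discharge, participants will be prescribed dipyrone 1g orally every 6 hours for 5 days" and closes with "Participants reporting anti-inflammatory or corticosteroid use will be excluded from statistical analysis, and the case will be documented and discussed". Corticosteroids are thus named twice alongside anti-inflammatories, as a class of their own. The removal rule gives no date from which use counts.
- **Timing (sections 4.7 and 4.12).** "The allocation envelope will be opened 24 hours after the surgical procedure when the PBM device is delivered". Treatment begins at the same point: "Applications will commence 24 hours after surgery and will continue daily throughout the experimental period".

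For the emergency room, section 4.8 says only "All patients will receive treatment according to the hospital's standard protocol" and does not list the drugs used there. No section limits the time from trauma to surgery.

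**The concern.** A drug criterion at entry and a rule that removes drug users from the analysis should fit together. Whatever will disqualify a patient from the analysis, and can be known before allocation, should be settled before allocation. Here the two rules differ in class (one against two) and in period (five days ending at the trauma, against no stated period).

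A patient may therefore satisfy the entry drug criterion, take one of 42 randomised places, use a device and contribute 12 weeks of visits, and then be left out for a fact available on the ward. There is also an ambiguity. Because the period of the section 4.9 rule is not stated, two analysts could apply it differently to the same patient and arrive at different analysis sets.

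**Working it through.** This is mainly a comparison of passages. The only arithmetic is the timeline and an illustration of what lost patients cost.

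**1. Drug class.** Entry: anti-inflammatories. Analysis: anti-inflammatories or corticosteroids. Because section 4.9 lists the two separately, the Protocol's own vocabulary does not place corticosteroids inside the first term.

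**2. Period.** Let D be the days from trauma to surgery. D is not stated, so 0 to 14 is assumed for illustration. Allocation falls at D + 1 days after the trauma.

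- D = 0: the entry window closes 0 + 1 = 1 day before allocation.
- D = 7: 7 + 1 = 8 days before.
- D = 14: 14 + 1 = 15 days before.

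No drug criterion covers those days. They are an upper limit on the exposed time, because section 4.9 rules out prescribing either class during the hospital stay. What remains is use before arrival, any use under the unlisted emergency-room protocol, and a patient's own continuing medication.

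**3. Two patients followed through the text.**

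| Patient | Entry drug criterion | Section 4.9, no time limit | Section 4.9, after discharge only |
| --- | --- | --- | --- |
| Corticosteroid use continuing from before the trauma | Met, since the class is not named | Randomised, then removed | Randomised, then removed if the continuing use is reported |
| Anti-inflammatory use between trauma and allocation only | Met, since the window ends at the trauma | Randomised, then removed | Randomised and analysed; the use is not addressed |

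The first patient is removed on either reading. The second is removed on one reading only.

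**4. What lost patients cost.** Section 4.5 gives 42 participants (21 per group), 90% power, a significance level of 0.05 and 15% loss. It gives no mean difference or standard deviation, so the 42 cannot be reproduced. The loss step can be approximated: 21 × 0.85 = 17.85, about 18 evaluable per group. Assume that 18 per group gives 90% power, two-sided 0.05, normal approximation. The implied standardised difference is (1.960 + 1.282) × √(2/18) = 1.08. Power with n per group is Φ(1.08 × √(n/2) − 1.960), computed with the unrounded 1.081:

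| Evaluable per group | Power |
| --- | --- |
| 18 | 90% |
| 17 | 88% |
| 16 | 86% |
| 15 | 84% |
| 14 | 82% |

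Each further patient lost per group beyond the planned loss costs about 2 percentage points. How many patients the mismatch would remove is not known, so the table is a scale and not an estimate.

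**The case against.** **The section 4.9 sentence is about the time after discharge.** It closes the discharge paragraph, follows advice on what to take at home, and is followed in section 4.13 by daily calls recording analgesic use. This is its most natural reading, and on it nobody is removed for use confined to the days between trauma and allocation. That much stands. It does not rescue the continuing corticosteroid user, who can still be reporting use after discharge, and it leaves the pre-allocation days unaddressed.

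**Corticosteroids are anti-inflammatory drugs.** Someone screening patients might apply the entry criterion to them. Section 4.9 speaks against this by naming them separately, but the objection has some force. The exclusion of systemic conditions that complicate the postoperative course may also catch some long-term users. Both points make the case rarer without closing the gap.

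**The gap is narrow.** In-hospital prescribing is already barred, and patients are recruited on presenting to the emergency room. This is correct and is allowed for above.

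**Stronger readings a reader might infer, which the Protocol does not support:**

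- *That these removals bias the randomised comparison.* Use fixed before allocation cannot depend on the arm, and removing on that fact by the same rule in both arms costs precision, not validity. Removal for use that begins after randomisation is a different matter and is not the point made here.
- *That the criterion turns away patients whose use no longer matters.* This needs the delay to surgery and the duration of drug effect, and neither is given. With surgery on the day of trauma, the barred use lies only 1 to 6 days before allocation.
- *That a particular number of the 42 would be lost.* No frequency of use is given, so any such count would be a guess.

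**Conclusion.** The point holds as a mismatch between two passages that should agree. The entry criterion covers one drug class up to the trauma; the analysis rule covers two classes over an unstated period; allocation lies later than the end of the entry window. For continuing corticosteroid use, randomisation followed by removal follows from the text on either reading of section 4.9, provided that corticosteroids are taken as the separate class section 4.9 makes them, that no other exclusion applies, and that the use is reported. For anti-inflammatory use between trauma and allocation, it follows only if section 4.9 has no time limit.

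The consequence is an avoidable loss of precision and an analysis set that is not uniquely defined. The size cannot be stated from the Protocol. The matter is worth correcting because the trial is small and the mismatch affects who is randomised, which no later analysis document can repair.

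**What to change.** 1. Reconcile the exclusion list in section 4.4 with section 4.9 so that both name the same drug classes.
2. State the period the entry criterion covers, up to allocation. Its length and reference point are for the investigators to set on clinical grounds.
3. Check the criterion before the envelope is opened at 24 hours after surgery, and record the answer.
4. State in section 4.9 which period its rule covers, and that it does not remove a randomised participant from the analysis for use that pre-dates allocation.

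The cost is one reworded criterion, one question on the first postoperative form and one added sentence. The downside is a few more patients found ineligible before allocation, which may slow recruitment slightly; those places then go to patients who will be analysed.
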